### Data sources

The study will constitute secondary analyses of antibiotic prescribing data from NHS England covering the period 2013 to 2018. CCGs were established in England in April 2013 following the Health and Social Care Act 2012.^33^ Data on antibiotic prescribing in primary care at CCG level will be sourced from the NHS England Antibiotic Quality Premium Monitoring Dashboard, which is produced by the NHS Business Services Authority (BSA).^34^ Primary Care prescribing data are publicly available from the NHS BSA website. The dataset contains the number of antibiotic items (STAR-PU) prescribed in each CCG from the financial year 2015/2016 to 2018/2019, with data for October 2018 the latest at the time of this protocol. Data for the period 2013 to 2015 will be mapped to CCG level from the practice-level data.

Practice-level antibiotic prescribing data will be sourced from OpenPrescribing, an Evidence-Based Medicine DataLab project by the University of Oxford. OpenPrescribing publishes monthly antibiotics prescribing data from August 2013, with data for October 2018 the latest at the time of this protocol. Practice-level antibiotic prescribing data from OpenPrescribing is not STAR-PU weighted, so the extracted data will be STAR-PU weighted using figures from the 2013 Item-based age–sex weighting for oral antibacterials^14^ and the number of registered patients in each age–gender category in a practice for each specific month.

Overall, the dataset offers coverage of at least 3 years postintervention given that antibiotic prescribing became a QP priority in March 2015. This will be important in investigating the immediate direct and indirect effects of the QP initiative while giving an insight into the sustainability of the identified effects (if any) in the long-term.

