### Statistical analysis

Our first analysis will be an interrupted time series to investigate whether antibiotic prescribing rate in England has changed over time, and how such changes, if any, are associated with the QP implementation in March 2015. This will be conducted using the ordinary least square regression method^41^ to assess whether the 2015/2016 QP establishment resulted in a shift in the level and trend in antibiotic prescribing in primary care in England compared with the period before the intervention. Using the practice-level dataset, a univariate time series with the mean antibiotic items (STAR-PU weighted) prescribed in all primary care practices in England for each month will be conducted using the *ITSA* function on Stata, with post-trend specification to show a postintervention trend. The Cumby-Huizinga general test for autocorrelation will be used for general specification test of serial correlation in the time series data.^42^

A new QP guideline was implemented each financial year with changes in the prescribing rate target and the proportion that improved prescribing constituted in the QP award for each year. Our mediation analyses will investigate the effects of the QP by comparing antibiotic prescribing rate in the financial year before its implementation to each subsequent year postimplementation; as such, our dataset for the mediation analyses will have the control group as the financial year before QP and the intervention group as a specific post-QP implementation year. Three analyses will be conducted for each of the three financial years since QP establishment. This will enable us to compare the effects of the different target levels that have been set over the years and the proportions of the QP award attributed to improvement in antibiotic prescribing.

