Using a unified model for the natural direct and indirect effects,^31^ we will investigate the relationship between the QP initiative, the potential mediators and antibiotic prescribing rate with adjustment for the practice and CCG characteristics. This approach addresses the issues associated with the traditional approach to mediation analysis that obtains natural direct and indirect effect estimates through a non-trivial combination of parameter estimates from multiple models for the regression of the mediator and that of the outcome.^32 43^ Also, the unified model is applicable to nonlinear regressions, different measurement types for outcome and mediator variables, and allows for interaction between the exposure and the mediator.^31^

We will first fit single-mediator models with each mediator separately modelled using the *medeff* function in Stata.^44^ With the single-mediator models, we will be able to establish the individual influence of each potential-mediator variable. Variables that showed a mediating effect in the single-mediator models will be added to build a multiple-mediator model using a sequential mediation analysis method.^45^

A sequential multiple-mediator analysis is preferred to merely summing the effects of the single mediators because the sum may differ from the joint mediated effect, particularly as our potential mediators may influence one another.^45^ Modelling all the significant mediators together provides a more accurate assessment of the mediation effects and causal relationship,^46 47^ while assessing the indirect effect of a group of mediators in explaining how and why the intervention impacts on the outcome. The ordering of the mediators in the sequential mediation analysis will be based on evidence from the literature and the outcome of our stakeholders’ workshop designed to identify possible pathways between the predictor, mediators and outcome. The workshop that will validate our conceptual model will also enable us to identify what mediators affect one another and inform interactions to include in our model. All analysis will be conducted in the Stata statistical package V.15.1.

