### Sensitivity analyses

Sensitivity analyses using dummy implementation dates of 1 to 3 months before and after the actual month each of the QP guidance were published will be conducted to assess the difference between the time the guidance is published and the dissemination of information and development of local arrangements by the CCGs. These analyses will further help to investigate the anticipatory effect of the policy and whether lag in implementation attenuates the effect of the intervention.

Also, we will conduct separate analysis with the outcome variable (antibiotic prescribing rate) as a binary variable (indicating whether each CCG achieved the required rate of reduction in antibiotic prescribing as stated in the QP guidance for each year) to examine whether the classification of the outcome variable based on achievement of QP target influences the results.

Subgroup analyses will be conducted on clusters of primary care practices based on their antibiotic prescribing behaviour (high and low prescribers) and indices of deprivation to examine whether any effect of the QP initiative seen in the overall population is different in subgroups of practices. The top and bottom 20% antibiotic prescribers as of March 2015 will be categorised as high and low prescribers. To address the issue of regression to mean in subgroup analyses, we will build a separate model with categorisation into high and low prescribers based on the mean of the prescribing rate of practices in the last 3 months to March 2015. The use of mean of multiple measures will offer a better estimate of each practice’s true mean before the 2015/2016 QP initiative.^48^ The subgroup analysis based on the indices of deprivation data^36 49^ at primary-care practice level will be important in establishing the equity impact of the QP initiative.

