## Limitations

This study has some limitations. The survey that provided data on mediator variables included 187 of the 209 CCGs existing at the time of the study. However, this sample size is large enough for strong statistical power, and multiple imputation will be used to address issues on missingness. Furthermore, due to the limited data on practice-level interventions or strategies that might potentially mediate the effect of the QP on antibiotic prescribing, we will not be able to extensively investigate the mechanism of QP impact at the practice level. Nevertheless, extensive investigations will be conducted at CCG level where we have more data on potential mediators.

In 2013, the Primary Care Trusts in England, which were responsible for planning and commissioning healthcare services at the primary care level, were transformed to CCGs.^50^ As such, our investigations are restricted to the CCG era. This is important as the QP initiative is implemented and rewards paid out at CCG level.

We recognise that the causal interpretation of any effect from our mediation analysis rests on assumptions such as sequential ignorability and exchangeability. Causal inference from this analysis will be limited given that our data are observational with the absence of random assignment of cases to treatment and mediator levels, as well as the likelihood of unmeasured confounders. The rate of consultation for conditions where antibiotics might be prescribed is one of the unmeasured confounders in our study. This has not been accounted for in our analyses as these data are not available nationally at the practice level.

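### The subgroup and equity questions are framed as subgroup versus overall population; a claim of a different QP effect should rest on a direct contrast between subgroups

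*Protocol article*

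**What the plan says.** Under Sensitivity analyses, the protocol article runs subgroup analyses on clusters of practices defined by prescribing level and by deprivation. The stated purpose is "to examine whether any effect of the QP initiative seen in the overall population is different in subgroups of practices".

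The prescribing groups are fixed: "The top and bottom 20% antibiotic prescribers as of March 2015 will be categorised as high and low prescribers". To deal with regression to the mean, a second definition uses the three months to March 2015: "we will build a separate model with categorisation into high and low prescribers based on the mean of the prescribing rate of practices".

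The deprivation analysis, according to the same section, "will be important in establishing the equity impact of the QP initiative".

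The Statistical analysis section describes the interrupted time series as "a univariate time series with the mean antibiotic items (STAR-PU weighted) prescribed in all primary care practices in England for each month", that is, one national series with no comparison group. The only interaction involving the exposure that it mentions is a property of the mediation approach, which "allows for interaction between the exposure and the mediator". An interaction of QP with subgroup is not mentioned.

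**The concern.** Two things in the text do not fit together. The comparator is the whole population, which includes the subgroup being judged. The conclusion drawn, an equity impact, is about how more deprived practices fared relative to less deprived ones. Setting a part against the whole does not estimate that quantity.

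If each cluster gets its own fit and the results are read side by side, two errors become possible. A reader may take a significant result in one group and a non-significant one in another as evidence that the effects differ, which it is not. In the other direction, seasonal and national events move all groups together from month to month. That shared movement inflates the standard error of every separate fit, although it cancels when one group is subtracted from another. A real difference between deprivation groups could then be reported as a similar effect.

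The Discussion says that the results are meant to inform the future of the incentive, so either error would matter.

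**Working it through.** The article gives no alpha, power, effect size or variance for the subgroups, so there is no figure of its own to reproduce. Everything below rests on a two-sided 5% level and on the other assumptions stated.

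**Inputs from the article**
- Series length (Data sources): "OpenPrescribing publishes monthly antibiotics prescribing data from August 2013, with data for October 2018 the latest at the time of this protocol". August 2013 to October 2018 is 63 months. Counting up to and including March 2015 gives 20 before QP and 43 after.
- Prescriber subgroups (Sensitivity analyses): a fraction f = 0.2 of practices each. The middle 60% is in neither.

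**1. What the overall comparator measures.** Write S for the effect in the subgroup and R for the effect in the rest. The overall effect is fS + (1 − f)R, so subgroup minus overall is (1 − f)(S − R). For f = 0.2 this is 0.8 × (S − R). The rest mixes the opposite 20% with the middle 60%. This is therefore a diluted contrast against a mixture, and not high versus low.

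**2. False differences depend on a rule that the article does not state.** Suppose the true effects are equal.
- Rule: significant in one of two independent subgroups but not in the other. The probability is 2p(1 − p), where p is the power in each subgroup: 50% at p = 0.5, 32% at 0.8, 18% at 0.9, 9.5% at 0.95 and 2% at 0.99.
- The same rule, simulated on 63-month series with shared noise at twice the subgroup SD: 21% at about 50% power and 15% at about 80% power.
- Rule: overall estimate outside the subgroup's 95% CI, practices independent. The true variance of the difference is proportional to 1/f − 1 = 4, and the interval uses 1/f = 5. The rate is P(|Z| > 1.96 × √(5/4)) = 2.8% per subgroup, and 5.5% that either the high or the low group is flagged.
- Direct contrast between two subgroups: 5%.

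**3. Missed differences.** Assume independent monthly errors, subgroup-specific SD 1 and shared SD 2, and a least-squares model with level and trend change. With 20 and 43 months, the standard error of the level change is 0.553 times the error SD.
- Direct contrast (shared noise cancels): error SD √(1 + 1) = 1.414, so SE = 0.553 × 1.414 = 0.78.
- Two separate fits treated as independent: each has variance 1 + 4 = 5, so the combined SD is √10 = 3.162 and SE = 0.553 × 3.162 = 1.75 (1.74 in simulation).
- Ratio: √(10/2) = 2.24. The trend change has the same ratio.

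A true difference that the direct contrast detects with 79% power is detected from separate fits in 51% of simulated studies at shared SD 1, and in 7% at shared SD 2.

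**4. Regression to the mean in the prescriber groups.** For the top and bottom 20%, the spurious gap is 2 × 1.40 × (1 − reliability) in SD units. Single-month reliability is not given; take 0.6 to 0.95.
- One month: 2 × 1.40 × 0.40 = 1.12 down to 2 × 1.40 × 0.05 = 0.14.
- Three-month mean, reliability 3ρ/(1 + 2ρ) = 0.818 to 0.983: a gap of 0.51 down to 0.05.

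Averaging shrinks the artefact but leaves some of it, and a direct high-minus-low contrast does not remove it.

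**The case against.** The strongest reply is that the article never says a between-subgroup test will be left out. It states a purpose in ordinary wording for a heterogeneity question, and a condensed article may leave the interaction term to a fuller plan. That stands: a reader might infer that no such test will be done, but this would be an inference from silence. What the article does state is the comparator and the equity conclusion attached to it, and those are what this point concerns.

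A reader might also infer that equal effects will often be reported as different. The document does not support that. It needs the rule of significance in one group and not in another, which appears nowhere, together with low to moderate subgroup power. Power cannot be computed, since neither the number of practices nor their variance is given. The remark that "this sample size is large enough for strong statistical power" concerns the CCG survey. Comparing estimates with the overall estimate gives only 2.8% per subgroup. With shared noise, comparing separate estimates as if independent is very conservative: false positives are about 0.7% at shared SD 1 and 0.01% or less at SD 2. The sturdier risk is therefore the missed difference.

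Two further replies also stand. The article does recognise regression to the mean and takes a step against it. And a log scale, a ranking of the subgroups or a softer verb for the equity statement would be matters of preference; this point does not depend on them.

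**Conclusion.** The point holds in a limited form. The subgroup and equity questions are set up against a population that contains each subgroup, and the contrast that would answer them is not named. Reading separate fits side by side can create a difference or hide one. The frequency of false differences cannot be derived from the document.

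The loss of precision is about 2.2-fold (standard error 1.74 against 0.78) if shared monthly noise has twice the subgroup SD. It is √2, or 1.4-fold, if the two SDs are equal, and nil if no noise is shared. These figures assume independent monthly errors, equal subgroup variances and a segmented regression in each subgroup; the article does not say which model the subgroup analyses use.

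A direct contrast is well suited to deprivation, where the groups are not formed from the outcome. For high and low prescribers it helps with precision but does not cure the selection on the outcome.

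**What to change.** State that any claim of a differential or equity effect will rest on a direct contrast: most versus least deprived practices, and high versus low prescribers. Fit either a multiple-group interrupted time series with the software already planned, or a single-group model to the monthly difference between the two groups. Report the difference in level change and in trend change, each with its 95% CI. Subgroup-specific and overall estimates can still be shown, as description.

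Treat deprivation as the cleaner contrast. Add a sentence that the high-versus-low-prescriber contrast remains subject to residual regression to the mean, even with the three-month categorisation.

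The cost is one extra model per subgroup pair, on data already being collected, and a few lines of text.

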Interventions such as antibiotic stewardship programmes, education and training initiatives targeted at prescribers and patients, financial incentives, among others have been implemented in England to reduce AMR through reduced prescribing. In particular, the Quality Premium (QP) is a National Health Service (NHS) England initiative established in 2013 to reward Clinical Commissioning Groups (CCGs) financially based on the quality of specific health services considered to be of national or local priority and commissioned over a specific period.^17^ Improvement of antibiotic prescribing in primary care was one of the national priorities in the 2015/2016 guidance,^18^ constituting 10% of the premium awarded from 2016/2017 to date.^19 20^ Key aspects of the ‘improved antibiotic prescribing’ priority are reductions in the number of antibiotics prescribed in primary care facilities across England and in the proportion of broad-spectrum antibiotics prescribed in primary care (2015–2017).^19^ Part of the requirements in the 2015/2016 QP guidance for demonstrating improved antibiotic prescribing by CCGs was a reduction in the number of antibiotics prescribed in primary care by 1% of the mean value in England in 2013/2014 (ie, 1.61 items per Specific Therapeutic group Age-sex Related Prescribing Unit (STAR-PU)). This was further increased to 4% in the 2016/2017 guidance.

Emerging evidence suggests a reduction in antibiotic prescribing in primary care practices in the UK following the QP initiative.^21 22^ Prescribing data from England show a reduction of about 2.7 million antibiotic items between 2014/2015 and 2016/2017 financial year.^23^ Eighty-eight per cent of the CCGs in England achieved the target of reducing antibiotic prescribing in the first 2 years of QP.^21^ Also, there has been a significant reduction in the proportion of broad-spectrum antibiotics prescription with 83% of the CCGs meeting their target in the first 2 years.^21^ Such reductions in antibiotic prescribing would be expected to contribute to reductions in the development of resistance.^24^ However, little is known about the mechanisms by which the QP initiative impacted on antibiotic prescribing in primary care practices.

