### Variables

The predictor will be a binary variable indicating the implementation of the QP intervention. The intervention will include all periods after March 2015 when the 2015/2016 QP guidance in England was published, while the control will be periods prior to this. The primary outcome of interest is the rates of antibiotic prescribing at CCG level in England, which will be a continuous variable indicating the number of items (per STAR-PU) prescribed per month.

To account for differences in practice and CCG characteristics that can contribute to variance in antibiotic prescribing, we will be adjusting for the number of general practitioners in each practice (from the NHS Workforce data),^35^ the index of multiple deprivation (from the Department for Communities and Local Government),^36^ prevalence of comorbidities (asthma, chronic obstructive pulmonary disease, diabetes, cancer, chronic kidney disease (from the NHS Quality and Outcomes Framework database)),^37^ the prescribing rate of other non-antibiotic drugs (opioids and benzodiazepines) and seasonal influenza vaccination rate (from PHE).^38^

Mediator variables will be derived from the questionnaire data from a PHE survey,^39^ with 187 of the 209 AMS leads representing CCGs in England and data from other organisations that have evaluated the interventions treated as potential mediators in this study. In the PHE survey, participants were required to complete questionnaire items, which included their adoption of national and local strategies in their respective CCG to enable them to meet QP targets on antibiotic prescribing in primary care. The mediator variables will be binary or continuous variables, indicating the adoption of key interventions and intermediaries that are hypothesised to reflect in the integration of the QP guidance in improving antibiotic prescribing in primary care practices.

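### Defining high and low prescribers on months that stay in the pre-QP baseline leaves regression to the mean in the subgroup contrast; averaging three of those months does not remove it

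*Protocol article*

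**What the plan says.** The protocol article, under Sensitivity analyses, plans subgroup analyses by prescribing level and by deprivation. Their purpose is "to examine whether any effect of the QP initiative seen in the overall population is different in subgroups of practices". The main rule for prescribing level is: "The top and bottom 20% antibiotic prescribers as of March 2015 will be categorised as high and low prescribers". The article names regression to the mean as a problem and answers it with a second model, using "categorisation into high and low prescribers based on the mean of the prescribing rate of practices in the last 3 months to March 2015". Its reason for this is that "The use of mean of multiple measures will offer a better estimate of each practice’s true mean before the 2015/2016 QP initiative".

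Two other sections fix the comparator. Under Variables: "The intervention will include all periods after March 2015 when the 2015/2016 QP guidance in England was published, while the control will be periods prior" (that is, months before publication). Under Statistical analysis: "our dataset for the mediation analyses will have the control group as the financial year before QP", which is April 2014 to March 2015. January and February 2015 are therefore baseline months on any reading, and March 2015 is one under the financial-year definition. No section removes the classifying months from the baseline or sets a separate window for classification.

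**The concern.** A practice enters the top fifth partly because its stable level is high and partly because its noise was high in the classifying months. That noise is not repeated later. If the classifying months are also baseline months, the high group's baseline is too high and the low group's too low, and both drift back after March 2015 even if QP did nothing. The classifying months are also the last before the break, where they weigh most on a segmented regression.

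At stake is the question the subgroup analysis asks: whether QP worked differently in high and low prescribers. Both planned models classify on months in the same baseline, so agreement between them would not be evidence that the problem is absent.

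**Working it through.** The documents give no figure for regression to the mean, so there is none to reproduce. The article does not say which model the subgroups use, so both planned before-after contrasts are checked.

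**Inputs from the article.** Top and bottom 20% (Sensitivity analyses). Monthly practice data: "OpenPrescribing publishes monthly antibiotics prescribing data from August 2013, with data for October 2018 the latest at the time of this protocol" (Data sources), which gives 20 months to March 2015 and 43 after. Yardstick: the 2015/16 target was "a reduction in the number of antibiotics prescribed in primary care by 1% of the mean value in England in 2013/2014", raised to 4% in 2016/17 (Introduction).

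**Assumptions, not in the documents.** No QP effect. Monthly rate = stable practice level + noise. Between-practice SD 20% of the mean. Monthly noise SD *s* from 4% to 20%. Month-to-month noise correlation 0, 0.6 or 0.8. March 2015 is the last baseline month.

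**Why the range starts near 4%.** If 1.61 items per STAR-PU is an annual figure, a month averages 1.61/12 = 0.134. For assumed practices of 1,000, 2,000, 4,000 and 6,000 STAR-PU, Poisson noise alone is 8.6%, 6.1%, 4.3% and 3.5%. Real noise can only be larger.

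**Formula.** The expected noise carried by the top fifth in month *t* is 1.400 × Cov(noise in *t*, S) / SD(S). S is the classifying value, and 1.400 is the mean of the top fifth of a standard normal. The low group is the mirror image.

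- Annual contrast (2015/16 minus 2014/15), independent noise: minus the sum of the carried noise over the baseline year, divided by 12.
- Level change in segmented OLS: baseline month *j* (0 to 19) has weight 1/20 + (20 − 9.5)(*j* − 9.5)/665. January, February and March 2015 get 0.168, 0.184 and 0.200, together 0.553 before rounding.

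**Worked case, s = 10%, independent noise.**

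- March rule: SD(S) = √(400 + 100) = 22.36. Carried noise = 1.400 × 100/22.36 = 6.26%, in one month. Level = −0.200 × 6.26 = −1.25%. Annual = −6.26/12 = −0.52%.
- Three-month rule: SD(S) = √(400 + 33.3) = 20.82. Carried noise = 1.400 × 33.3/20.82 = 2.24%, in each of three months. Level = −0.553 × 2.24 = −1.24%. Annual = −3 × 2.24/12 = −0.56%.

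Averaging cuts the noise per month but puts it in three baseline months. With independent noise the covariance of S with the 12-month baseline mean is s²/12 under both rules. The divisor SD(S) is smaller for the three-month mean, so the annual bias is slightly larger.

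**False change in the high group, % of the overall mean**

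| s | Level, March, corr. 0 | Level, 3-month, corr. 0 | Annual, 3-month, corr. 0 | Level, March, corr. 0.6 | Level, 3-month, corr. 0.6 | Level, earlier window, corr. 0.6 |
|---|---|---|---|---|---|---|
| 4 | −0.22 | −0.20 | −0.09 | −0.34 | −0.46 | +0.05 |
| 6 | −0.48 | −0.46 | −0.21 | −0.76 | −1.02 | +0.11 |
| 8 | −0.83 | −0.80 | −0.36 | −1.30 | −1.78 | +0.20 |
| 10 | −1.25 | −1.24 | −0.56 | −1.96 | −2.71 | +0.31 |
| 15 | −2.52 | −2.66 | −1.20 | −3.95 | −5.61 | +0.66 |
| 20 | −3.96 | −4.47 | −2.02 | −6.20 | −9.05 | +1.09 |

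**Earlier window.** This classifies on August 2013 to March 2014 and fits from April 2014. With independent noise the false change is exactly 0 in both contrasts. With correlation 0.8 and s = 10%, the false 2015/16 change is −0.49% (March), −1.21% (three-month) and −0.98% (earlier window). The false level change is −2.42%, −3.26% and +0.39%.

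**Simulation.** With 7,000 practices (assumed), independent noise making up a fifth of the total variance and no effect, the high-low contrast in annual change was rejected in every run under both planned rules, and in 5% of runs with the earlier window.

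**The case against.** The authors saw the problem and acted on it. Their claim that a mean of several months estimates a practice's true level better is correct, and averaging does shrink the excess in the classifying months themselves (6.26% to 2.24% per month in the worked case). This stands as a point about labelling. It does not answer the before-after contrast.

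The size is unknown, and this stands too. At 4% independent noise the artefact is only 0.2% in level and 0.1% in annual change, well below the 1% target.

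A reader might infer that the plan will show QP working in high prescribers and backfiring in low prescribers even if it did nothing. The documents do not support that. The artefact adds to whatever really happened, and the Introduction reports a national fall of about 2.7 million items, with 88% of CCGs meeting the reduction target. A small artefact would shrink the fall in low prescribers, not reverse it.

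A reader might also infer that the three-month mean is simply worse than March alone. That is clear only if the noise is autocorrelated. With independent noise the two rules are about equal.

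Finally, the scope is narrow: one subgroup analysis among the sensitivity analyses.

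**Conclusion.** The point holds as a fault in a stated remedy. The classifying months lie in the pre-QP comparator under both rules, and averaging them leaves the selected noise there. The direction of the bias follows from the design: it exaggerates the high-low difference, and both planned models carry it the same way.

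The size cannot be fixed from the documents. On the assumptions above, the three-month rule gives a false level drop in high prescribers of about 0.2% to 4.5% with independent noise and about 0.5% to 9% with correlation 0.6. The false first-year change is about 0.1% to 2.0% with independent noise. Over much of that range the artefact is comparable with the 1% and 4% targets. At the low end it is minor.

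The national series, the CCG-level outcome and the deprivation subgroups are unaffected.

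**What to change.** For the prescriber-level subgroups only, classify practices on an earlier window already in the data, for example August 2013 to March 2014. Leave those months out of the fitted series, so that the baseline is April 2014 to March 2015. Leaving them out matters: if they stay in, a false level change of the opposite sign appears. Keep the March 2015 and three-month classifications as sensitivity analyses, described as subject to regression to the mean.

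The change is one of wording and needs no new data. It leaves 12 pre-QP months instead of 20, a single seasonal cycle, for estimating the prior trend in these subgroups.

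The plan should also state the limit of the remedy. It removes the artefact if monthly noise is independent, and most of the false level change if noise is autocorrelated. With strongly persistent noise (correlation 0.8) an annual bias remains, and in the first-year comparison it can exceed that of the March rule (−0.98% against −0.49% at 10% noise).
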